**Fig. 2 Fig2:**
[figure not shown]
Trial schedule

District hospitals that have not yet received EENC coaching will receive coaching before randomisation. Pre-coaching evaluation will be done to measure determinants of EENC performance and knowledge related to neonatal care before the introduction of EENC.

After the coaching, the districts will be randomly allocated into two groups. A research team member will distribute and explain a structured questionnaire to be filled out by the district participants to measure determinants of EENC performance and will administer written and simulation tests to measure EENC knowledge and skills. The collected data will be used as baseline data.

District hospitals that are allocated into the intervention group will receive a half day of on-the-job training on self-managed continuous monitoring. A research staff member will explain the concept, schedule, procedure and checklists of self-managed continuous monitoring.

After randomisation, district hospitals in the intervention group will conduct self-managed continuous monitoring and submit quarterly reports to the province. In the control group, provincial supervisors who are not involved in the research will visit districts every three months to supervise implementation of EENC and give feedback to district health workers.

Study participants will be monitored until one year after entry into this study or withdrawal from the study for any reason. The date of the final evaluation will be determined once a schedule for enrolment is set for each district. We will allow a variation of a month around the endpoint for timing of the final evaluation. The outcome data on participants who withdraw from the study before one year will be collected at the time of withdrawal.

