##### Potential confounders

We will collect participants’ demographic data such as age, sex, ethnicity, title, position and professional experience at baseline. A self-administered questionnaire will be used (Additional file 6). Data on those who discontinue participation will be collected at the time of dropping out.

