#### Data analysis

To ensure that cluster randomisation is successful, the significance of differences between the intervention and control groups for the baseline characteristics of participants such as age, sex, position, experience in years will be examined using the chi-squared test and *t*-test.

The primary endpoint is the change in determinants of EENC performance (behaviour change) from baseline to one year after randomisation. We expect a larger increase in the score of determinants of EENC performance in the intervention group than in the control group. The difference between the two groups will be examined based on an intention to treat (ITT) principle with the full analysis set. The imputation of missing data will be performed using the last observation carried forward method (ITT/LOCF) and a multiple imputation method (ITT/MI) using chained equations under the assumption of missing at random.

We will use a linear random-effects mixed model employing the maximum likelihood method. We will perform a crude analysis and then adjust the results with baseline variables and other multiple variables. The same method will be used for analysing secondary outcomes such as changes in scores for skills and knowledge of EENC. Changes in the average score of the written and simulation tests between baseline and one year after randomisation will be compared between the intervention and control groups.

Sensitivity analyses will be planned using the per protocol set (PPS). A significance level of 5% with two tailed testing will be applied for all significance analyses. We will also perform subgroup analyses to assess whether the effect of self-managed continuous monitoring on EENC quality varies amongst the five main components of EENC (clean birth process, provision of warmth, support for early initiation and exclusiveness of breastfeeding, hygiene cord care and basic neonatal resuscitation).

All statistical analyses will be performed using SAS version 9.4 for Windows (SAS Institute, Cary, NC, USA).

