#### Ancillary and post-trial care

This study may impose time and mental burdens on participants, especially those in the intervention group because district hospitals in the intervention group must conduct self-managed continuous monitoring activities quarterly. However, EENC is expected to be routinely provided at every birth in Lao PDR. Therefore, introduction of EENC itself will not require participants to do additional work. We anticipate that the burden of additional questionnaires and exams on participants will be trivial. We will consider implementing refresher EENC coaching if there is an increase in neonatal deaths in district hospitals and if health workers have a lower level of knowledge and skills for EENC at the end of this study compared to the baseline.

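### Follow-up ends at withdrawal for any reason, so the one-year score is not sought from withdrawn staff who still work in the hospital and would agree to be measured

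*Protocol article*

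**What the plan says.** The article's Participant timeline section sets both the end of follow-up and what happens at that point. "Study participants will be monitored until one year after entry into this study or withdrawal from the study for any reason". "The outcome data on participants who withdraw from the study before one year will be collected at the time of withdrawal". The Potential confounders section has a similar sentence: "Data on those who discontinue participation will be collected at the time of dropping out". It sits beside the baseline demographic data, so it is not clear that it concerns outcomes.

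The Data analysis section fixes the target: "The primary endpoint is the change in determinants of EENC performance (behaviour change) from baseline to one year after randomisation". The comparison "will be examined based on an intention to treat (ITT) principle with the full analysis set". Missing values are handled in two ways: last observation carried forward (LOCF), and multiple imputation (MI) by chained equations under missing at random. A per-protocol analysis is planned as a sensitivity analysis.

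The questionnaire behind the primary score is scheduled immediately after randomisation and at 3, 6, 9 and 12 months. The knowledge and skills tests are also repeated at one year in both groups. The Ancillary and post-trial care section says: "This study may impose time and mental burdens on participants, especially those in the intervention group".

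**The concern.** The endpoint is a one-year quantity, and the intention-to-treat principle calls for it in every enrolled participant who can be measured. The timeline rule instead ends measurement on the day of withdrawal, whatever the reason. That is unavoidable for people who refuse further contact and hard to avoid for people who have left. It is avoidable for a third group: staff who leave the study but keep working in the same hospital and would still fill in a questionnaire. Both arms are delivered to the hospital as a whole, so such a worker remains in the allocated setting, and assessment takes place there at one year in any case.

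What is at stake is the meaning of the primary comparison for these people. An exit score is not a one-year score, and no imputation method can supply a one-year score that could have been collected and was not. The primary score measures attitude, norms, perceived control and intention. Discontent with the monitoring could plausibly affect both the score and the decision to withdraw.

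**Working it through.** **The text, side by side.**
1. Endpoint: change from baseline to one year, by intention to treat (Data analysis).
2. Follow-up: stops at withdrawal for any reason, with the outcome taken that day (Participant timeline).
3. No other section provides a one-year measurement for withdrawers. The Exclusion criteria remove only staff already scheduled to leave or retire.
4. Under LOCF, the exit score is the last observation and is carried to one year. Under MI, the one-year value can be imputed instead, but only under missing at random.

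**Inputs for scale.** From Sample size and power calculation: 15 hospitals of 15 workers, ICC 0.06, effect size 0.6, two-sided 5%, and a score spread of 6.86. The article calls 6.86 a variance but uses it as an SD (0.6 × 6.86 = 4.1 points), and it is used that way here. Assumed here: an 8 v 7 hospital split; a baseline-to-one-year correlation of 0.5, so that the change has the same SD as the score; all withdrawal shares, timings and score gaps.

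**The plan's own figure.** Design effect = 1 + 14 × 0.06 = 1.84. SE of the difference = 6.86 × √[(1.84/15) × (1/8 + 1/7)] = 1.24 points. Power at 0.6 SD is 86% with a t reference on 13 df, or 91% with a normal reference, against the stated 80%. The stated figure is therefore conservative and is not in dispute.

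**Illustration A: LOCF, unequal withdrawal.** Bias = (share withdrawing in the intervention arm − share in the control arm) × (exit score − score the person would have had at one year). Type I error comes from the noncentral t on 13 df with noncentrality bias/SE.

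| Withdrawal | Gap | Bias (points) | Share of the 5-point target | Type I error |
|---|---|---|---|---|
| 20% v 10% | 0.5 SD (3.43) | 0.34 | 7% | 5.8% |
| 30% v 10% | 0.5 SD (3.43) | 0.69 | 14% | 8.1% |
| 30% v 10% | 1 SD (6.86) | 1.37 | 27% | 17.6% |

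The sign follows the sign of the gap. If exit scores lie above the one-year scores, greater withdrawal in the intervention arm favours the intervention. If they lie below, the bias has the same size and works against it.

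**Illustration B: LOCF, equal withdrawal, effect building linearly over the year.** Diluted effect = 0.60 × [1 − w(1 − t)], where w is the share withdrawing and t the fraction of the year reached.
- w = 10%, t = 0.5: 0.60 × 0.95 = 0.57; power 83%.
- w = 20%, t = 0.5: 0.60 × 0.90 = 0.54; power 79%.
- w = 30%, t = 0.25: 0.60 × 0.775 = 0.465; power 66%.

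**Illustration C: equal withdrawal, loss of precision only.** With 12 of 15 measured per hospital, the design effect is 1 + 11 × 0.06 = 1.66 and the SE is 6.86 × √[(1.66/12) × (1/8 + 1/7)] = 1.32 points. Power at 0.6 SD falls from 86% to 82%.

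A and B describe LOCF and do not carry over to MI.

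**The case against.** The strongest reply is that the rule concerns withdrawal from the study, not reduced participation in its activities. A reader might infer that anyone who stops attending peer review or feedback sessions is no longer measured. The article does not say that. It plans a per-protocol analysis beside the intention-to-treat one, which suggests that non-adherent staff stay in the main analysis. This stands, and the point is limited to people who withdraw from the study.

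Second, the group may be very small. Planned leavers are excluded, directors are involved, and visits are scheduled so that participants are present. Setting aside leavers and refusers may leave few people. This also stands, and it limits the size of the problem.

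Third, a reader might infer that the rule biases the trial towards the intervention. The documents do not support a direction. The article expects scores to rise over the year, more so in the intervention arm, so an early score could as well be too low and dilute the effect. Nor do they show that missing at random fails. The burden is something that may arise, and the same section describes the burden of the extra questionnaires and exams as trivial. Differential withdrawal is foreseeable but not established.

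Fourth, the exit score adds information close to drop-out, and the analysis does not rest on LOCF alone. That is a reason to keep the exit score, but not a reason to forgo the one-year score.

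Last, a condensed article may leave withdrawal categories to the full protocol. An absent definition would be no finding. Here, however, the article states a rule that covers every reason for withdrawal and says when the outcome is taken.

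**Conclusion.** The point holds in limited form. The stated rule does not seek the one-year value from withdrawn staff who remain at the hospital and would agree to be measured, although the endpoint is defined at one year under intention to treat. LOCF then treats the exit score as the one-year score, and MI depends on missing at random, which is uncertain here.

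Neither the size nor the direction of any bias can be determined. The article gives no withdrawal rate; the withdrawal shares, their timing and the score gaps are all assumed. Within the assumed range, the effect under LOCF runs from a few tenths of a point (0.34 at 20% v 10% with a half-SD gap) to 1.37 points in the most extreme case, in either direction. With equal withdrawal, the effect is diluted by up to about a fifth (0.60 to 0.465). If few withdrawers remain measurable, the effect is small. It would go too far to say that the intention-to-treat analysis is invalid or that type I error is inflated. The change is worth making because it obtains data that cannot be recovered later and uses assessments already planned.

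**What to change.** Amend the Participant timeline rule along these lines: enrolled staff who stop taking part, or change post but remain at the hospital, are still asked to complete the one-year questionnaire and tests at the planned visit, unless they refuse further data collection. The score at withdrawal is collected as additional data and does not replace the one-year score. Reasons for withdrawal are recorded by arm. Staff who have left the hospital need not be traced.

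The cost is one changed rule, a matching line in the consent information, and a few more questionnaires and tests at visits already scheduled. The downside is that some of these staff will decline or answer less carefully, so some one-year values will still be missing.

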### Sample size and power calculation

The number of clusters, or district hospitals, is 15. We will recruit 15 health workers from each of the 15 district hospitals, 225 in total. This study is designed to detect at least a 5-point increase in the score for determinants of EENC performance (behaviour change) in the intervention group compared to the control group with 80% statistical power at a significance level of 0.05 using a 2-tailed test. There has been no previous cluster randomized studies carried out in Lao PDR. Therefore, we assume that the intra-cluster correlation coefficient (ICC) is 0.06 and that the effect size is 0.6 by referring to previous cluster RCTs in developing countries [26]. We examined the statistical power of this cluster size with this ICC and effect size. In previous studies that used the questionnaire of Planned Theory Behaviour, the largest variance in the score was 6.86 [27]. Given that variance, we expect to detect a difference of 4.1 points in the score for determinants of EENC performance with an effect size of 0.6, which is smaller than the 5-point difference we expect to detect**.** We, therefore, believe that this sample size is large enough to test the primary outcome.

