**Methods:**

A clustered randomized controlled trial was designed to compare the effectiveness of self-managed continuous monitoring with external supervisory visits to monitor health workers’ satisfactory EENC performance and their knowledge and skills related to the EENC in Lao PDR. Determinants of EENC performance will be measured with a structured questionnaire developed based on the Theory of Planned Behaviour, which predicts future behaviour. During self-managed continuous monitoring activities, health workers in each district hospital will conduct periodical peer reviews and feedback sessions.

Fifteen district hospitals will be randomly allocated into the self-managed continuous monitoring (intervention) and the supervision (control) groups. Fifteen health workers routinely involved in maternity and newborn care including physicians, midwives and other health staff will be recruited from each hospital (effect size 0.6, intra-cluster correlation coefficient 0.06, 5% alpha error and 80% power). We will compare the change in the mean score of the determinants before and one year after randomisation between the two groups. We will also compare the retention of knowledge and skills related to the EENC between the two groups. The expected enrolment period is July 20th, 2017 to July 20th, 2018.

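### The sample-size section calls 6.86 a variance but uses it as a standard deviation, so the stated 4.1-point detectable difference does not follow from the stated input

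*Protocol article*

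**What the plan says.** All the inputs are in the Sample size and power calculation section of the protocol article.

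- Sample: "We will recruit 15 health workers from each of the 15 district hospitals, 225 in total".
- Target in points: "This study is designed to detect at least a 5-point increase in the score for determinants of EENC performance", "with 80% statistical power at a significance level of 0.05 using a 2-tailed test".
- Clustering and standardised effect: "we assume that the intra-cluster correlation coefficient (ICC) is 0.06 and that the effect size is 0.6".
- Spread of the score: "the largest variance in the score was 6.86".
- Conversion to points: "Given that variance, we expect to detect a difference of 4.1 points in the score for determinants of EENC performance", at an effect size of 0.6.

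The section then notes that 4.1 is below 5 and concludes that the sample is sufficient for the primary outcome. The Methods paragraph of the abstract gives the same design inputs: "effect size 0.6, intra-cluster correlation coefficient 0.06, 5% alpha error and 80% power". The Data analysis section defines the primary endpoint as a change in the determinants score from baseline to one year.

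**The concern.** An effect size of 0.6 means 0.6 standard deviations. Multiplying it by a variance does not give a difference in points. The article prints both the input (a variance of 6.86) and the result (4.1 points), and they disagree by a factor of √6.86 = 2.62. At least one of them is wrong as written.

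The section's adequacy argument in points is the comparison of 4.1 with 5, so the reader needs to know what 4.1 is. The label also decides how large the targeted benefit is: 5 points is a fairly large effect (0.73 SD) if 6.86 is an SD, and a very large one (1.9 SD, over three times the assumed 0.6) if it is a variance.

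**Working it through.** **Inputs.** From the sample-size section: 15 hospitals, 15 staff each, ICC 0.06, effect size 0.6, target 5 points, two-sided alpha 0.05, power 80%, spread 6.86. From the Trial design section: 1:1 allocation within strata. With 15 hospitals I take 7 v 8, which is an assumption.

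**Step 1. Reproduce the stated 4.1 points.** Difference in points = effect size × SD.

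| Reading of 6.86 | SD | 0.6 SD in points | 5 points in SD |
|---|---|---|---|
| Standard deviation | 6.86 | 0.6 × 6.86 = 4.116 | 5 / 6.86 = 0.73 |
| Variance, as written | √6.86 = 2.62 | 0.6 × 2.62 = 1.57 | 5 / 2.62 = 1.91 |

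Only the first row gives 4.1.

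**Step 2. Does the mislabel affect power?** Design effect = 1 + (15 − 1) × 0.06 = 1.84, so the effective total is 225 / 1.84 = 122.3. In SD units, the variance of the difference between arms is 1.84 × (1/105 + 1/120) = 0.03286, and the standard error is 0.1813. Power is from a noncentral t with 15 − 2 = 13 degrees of freedom; the normal approximation is shown beside it.

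| Difference | In SD | SD / 0.1813 | Power (t, 13 df) | Power (normal) |
|---|---|---|---|---|
| Effect size 0.6 | 0.60 | 3.31 | 86% | 91% |
| 5 points, SD 6.86 | 0.73 | 4.02 | 96% | 98% |
| 5 points, SD 2.62 | 1.91 | 10.5 | >99.9% | >99.9% |

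The first row does not use 6.86 at all. A 6 v 9 split gives 85% (t) or 90% (normal) at 0.6 SD. For 5 points to have only 80% power, the SD would have to be about 9.1 (t) or 9.8 (normal).

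**Step 3. Score or change (rests on an assumption).** The section describes 6.86 as the spread of a score, while the endpoint is a change. Suppose 6.86 is a single-time SD, equal at both times, and raw change is analysed with the same ICC. Then the SD of change is 6.86 × √(2(1 − r)), where r is the correlation between baseline and one year. The document gives no r, so a range is shown (t, 13 df, 7 v 8).

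| Assumed r | SD of change | Power for 5 points | Power for 4.1 points |
|---|---|---|---|
| 0 | 9.70 | 75% | 58% |
| 0.3 | 8.12 | 88% | 73% |
| 0.5 | 6.86 | 96% | 86% |

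Power for 5 points reaches 80% at r of about 0.12.

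**The case against.** The strongest reply is that nothing of substance changes. The number of hospitals is fixed at 15, and the section checks whether that sample is enough. The power at 0.6 SD does not depend on 6.86. If the word variance is wrong, one word needs replacing. If the word is right, the true difference at 0.6 SD is 1.6 points rather than 4.1, so the published figure understates what the trial can detect. The error is then conservative. All of this stands.

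Three stronger readings are tempting, and the document does not support them.

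- **That 80% power for 5 points fails to follow.** It does follow: power is 96% or more under either reading of 6.86.
- **That 86% at 0.6 SD shows the stated 80% to be wrong.** The 80% is a requirement, and exceeding it meets it.
- **That 0.6 SD and 5 points are conflicting targets.** The text asks for at least 5 points and relates the two itself: a sample adequate for the smaller difference is adequate for the larger. They would clash only if each had to carry exactly 80% power at the same SD of 6.86 or 2.62, which the text does not say.

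On score versus change, the reply is that r is unknown, that an article may leave this detail to the full protocol, and that the planned model is also to be adjusted for baseline variables. If those include the baseline score, the residual SD is 6.86 × √(1 − r²), which never exceeds 6.86, and power for 4.1 points is at least 86% at the same ICC. That is fair, so Step 3 is a caveat and not a finding of low power.

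**Conclusion.** The labelling or derivation error is real and can be checked from one paragraph. As written, a variance of 6.86 gives 1.6 points at an effect size of 0.6, not 4.1; the published 4.1 needs an SD of 6.86. The cited source is not available here, so which of the two is wrong remains open.

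A reader might infer that the trial is underpowered. The calculation does not show that: the 80% requirement is met at 0.6 SD and at 5 points, given ICC 0.06, 15 analysed staff per hospital, a 7 v 8 split, and 6.86 as the spread of the outcome analysed. The last condition is the one the section leaves unclear. If 6.86 is a single-time SD and raw change is analysed, power for 5 points falls below 80% only when r is below about 0.12.

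Severity: minor; it should be fixed.

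**What to change.** 1. Look up 6.86 in the cited questionnaire study.
2. If it is an SD, replace the word variance with SD 6.86 and keep 4.1 points as 0.6 SD.
3. If it is a variance, write variance 6.86 (SD 2.62), restate the difference at 0.6 SD as 1.6 points, and reconsider the 5-point target, which would then be 1.9 SD.
4. In the same sentence, say whether the figure describes a single score or a change from baseline. If a single score, give the assumed correlation.

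The cost is one looked-up figure and one reworded paragraph. The number of hospitals, the number of staff and the planned analysis stay as they are.

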### Data collection, management and analysis

#### Data collection

Data will be collected from results of a questionnaire, written and simulation tests and checklists by central and provincial officials, who will have been trained prior to commencing the study. An in-depth interview of health workers is planned to take place at the final evaluation to identify key factors in the success of implementing activities related to the EENC.

